### Schedule of visits

All participants complete self-report and physiological measures upon study entry (T_1_), 9 weeks later (T_2_), and at 3 months postpartum (T_3_). The duration of the TAU follow-up assessments is based on the time needed for the MBCT group to complete the intervention. Because the highest incidence of new-onset postpartum mood disorders occurs between 2 and 3 months after delivery, the third study time point is at 3 months postpartum [3, 87]. The control group will be offered the MBCT intervention following the trial (at 3 months postpartum). Questionnaire pilot data will also be collected as it pertains to the feasibility, acceptability, and effectiveness of offering MBCT in the postpartum period.

### Primary, secondary, and other outcome measures

#### Primary psychological outcomes

*The Pregnancy-Related Anxiety (PRA)* scale is a 10-item scale used to examine the extent to which women are worried about their own and their baby’s health, labor, delivery and caring for a new baby. Items are rated on a scale ranging from 1 (*never or not at all*) to 4 (*a lot of the time or very much*). The scale has shown strong associations with maternal and infant health outcomes over and above other traditional measures of state and trait anxiety [7, 88]. This scale has been found to have acceptable internal consistency (Cronbach’s alpha = 0.79).

*The Edinburgh Depression Scale (EDS)* will be used to assess symptoms of depression experienced during pregnancy and the postpartum period. Higher scores indicate more depressive symptoms. The EDS has been validated against interview schedules and other self-report instruments and has good internal reliability [89].

*The Generalized Anxiety Disorder Scale (GAD-7)* will be used to screen for and assess the severity of generalized anxiety disorder (GAD). Higher scores indicate more symptoms of GAD. The GAD-7 has excellent reliability and good criterion and convergent validity [90].

*The Perceived Stress Scale (PSS-10)* will be used to assess symptoms of perceived stress. The PSS-10 has good reliability and validity [91]. Among pregnant and postpartum women, it has been found to have a satisfactory level of internal consistency, ranging from 0.71 to 0.83 [92, 93].

#### Secondary physiological outcomes

*Salivary cortisol* will be collected at home on 2 weekdays using the following schedule: upon waking, 30 min after waking, and at 20:00 h. Participants will receive individualized training on collecting samples during their first study. They will be given instructions to use Salimetrics Oral Swabs (SOS) to collect saliva samples and an app (mEMA, developed by Tefsoft, Inc.) to answer questions about the timing of sample collection and their current mood. In addition, the importance of adhering to the schedule will be emphasized.

*Stress reactivity.* At each of the three visits (baseline, post-treatment and, follow-up), participants from both groups will complete two stress tasks: a mental arithmetic and a Stroop task [64]. Each task will be followed by a 5-min recovery period. After the first recovery period, researchers will take 2 min to explain the second task. During the baseline period, subjects will be fitted with cardiovascular recording equipment and will sit quietly for 5 min. During the stress tasks and recovery periods, participant’s HRV and BP will be continually assessed. At the beginning of each stress task condition, participants will be instructed to respond as quickly and accurately as possible without making errors. These tasks reliably induce a stress response (REF) and have been used reliably in pregnancy.

*Mental arithmetic task*. During this 3-min task, participants will be presented with a series of mathematical subtraction equations with the answers included on a computer screen. They will be asked to determine whether the answer to each equation is correct or incorrect. Each correct answer is followed by a beep emitted from a speaker. Each incorrect answer is followed by a noxious blare emanating from the same speaker. The task was designed to change in difficulty according to the participant’s ability to maintain a 60 % correct answer rate [94].

*Stroop task.* During the Stroop task, participants are asked to correctly identify the color of the stimulus on a computer screen [95, 96]. During the 5-min stress period, participants will see a series of words (“red”, “green”, “blue”, “yellow”) on the screen and will be asked to correctly identify the color of the stimulus (i.e., the text) by using one of the keyboard buttons. Each correct answer is followed by a beep emitted from a speaker. Each incorrect answer is followed by a noxious blare emanating from the same speaker. Each task is followed by a 5-min recovery period. Order of the stress tasks will be fully counterbalanced across participants.

*Blood pressure and heart rate variability* will be assessed after a 2-min resting period at baseline by taking the mean of three seated measurements obtained during a 5-min baseline period. Systolic BP and diastolic BP (in mmHg) will be obtained at 1-min intervals during a 25-min period that includes baseline, stress tasks, and recovery periods. BP data is collected using an automatic, calibrated, oscillometric BP monitor (BpTRU Vital Signs Monitor, BpTRU Medical Devices, Coquitlam, BC, Canada). Electrocardiography (ECG) (BIOPAC MP36 system and BIOPAC MP36 Student Laboratory Program, BIOPAC Systems, Goleta, CA, USA) will be used to collect heart rate data, which in turn will be used to calculate HRV. Heart rate will be monitored on a beat-to-beat basis during baseline, stress tasks, and the two recovery periods. Three ECG leads will be placed: two leads on either side of the upper chest, equidistant from the heart, and one lead on the left side of the mid-abdomen.

*Subjective and objective sleep*. Subjective sleep quality and quantity will be assessed using the Pittsburgh Sleep Quality Index (PSQI). The PSQI consists of 19 self-rated items and five questions rated by the roommate or bed partner. There are seven components of the PSQI including: subjective sleep quality, sleep latency, sleep duration, habitual sleep efficiency, sleep disturbances, use of sleeping medications and daytime dysfunction [97]. The PSQI has good reliability and its validity has been confirmed by concurrent polysomnographic findings [97] and among pregnant women [98]. Self-reported sleep hours often do not accurately reflect objective sleep time [99]; therefore, in this study participants’ sleep will also be assessed using wrist actigraphy (Actiwatch II, Philips, Pittsburgh, OH, USA). Participants will be asked to wear an actigraph on their nondominant arm for 48 h at each assessment point. Data will be collected on weekdays to minimize the variability caused by potential differences in weekday and weekend sleep patterns. In order to accurately assess rest and sleep intervals, participants will also complete a sleep diary and note the times when they go to bed, nap, and wake up during the day on which they wear the actigrapher. The Actiware Software (Version 6.0.1) will be used to configure and download the data from the Actiwatches. Assessment of sleep with actigraphy has demonstrated sensitivity to treatment effects [100].

#### Exploratory outcomes

We will also collect information about the diagnosis of axis I disorders of the DSM-IV (using the Structured Clinical Interview for DSM-IV; SCID) at each study visit [86]. The DSM-IV, text revision (DSM-IV-TR) includes standardized diagnostic categories and criteria for the classification of mental disorders [101].

#### Demographic assessment

Demographic information will include marital status, ethnicity, age, family socioeconomic status (household income, education level, neighborhood characteristics of the home), working status, and number of children in the home. Health practices will be assessed via self-report and will include smoking, alcohol consumption, and level of habitual exercise. Assessment of previous mental health problems and assessment of psychotropic medication use will be assessed via interview.

### Risks to the safety of participants

To our knowledge, there are no known risks to the pregnant women involved in the experimental (MBCT) or control (TAU) conditions of the study. There is a mindful movement component of the intervention, and in the first session a handout about safe exercise in pregnancy is reviewed with all participants. Stress testing has been conducted in pregnant women without adverse events [102]. If any adverse events occur (e.g., increased suicidal ideation reported to the study therapist or other project staff) we have a treatment algorithm in place to triage participants to appropriate acute or long-term treatments, as needed to ensure participant safety. Adverse events will be reported by the research coordinator to the University of Calgary Ethics Review Board using a serious adverse event report.

### Sample size

Based on the findings from a previous study, which examined the impact of a MBI during pregnancy on prenatal stress and mood, we expected a medium effect size of Cohen’s *d* = 0.5 [44] for the outcomes of PRA, anxiety, and depression for pre-post testing. Using a two-tailed test and a .05 significance level, 21 participants in each group (42 total) would provide adequate power (95 %) to reject the null hypothesis [103]. With an estimated attrition rate of 20 %, the number of participants required becomes a minimum of 26 participants per group (total *N* = 52).

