**Methods:**

A randomized controlled trial (RCT) design with repeated measures will be used to evaluate the effectiveness of MBCT to treat psychological distress in pregnancy. A sample of 60 consenting pregnant women aged 18 years and above will be enrolled and randomized to the experimental (MBCT) or control (treatment as usual) condition. Primary (e.g., symptoms of stress, depression, and anxiety), secondary (cortisol, blood pressure (BP), heart rate variability (HRV), and sleep) and other outcome data (e.g., psychological diagnoses) will be collected via a combination of laboratory visits and at-home assessments from both groups at baseline (T_1_), immediately following the intervention (T_2_), and at 3 months postpartum (T_3_). Descriptive statistics will be used to describe sample characteristics. Data will be analyzed using an intention-to-treat approach. Hierarchical linear models will be used to test intervention effects on primary and secondary outcomes.

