### Statistical analyses

Baseline characteristics (demographic and psychological) will be compared between groups using *t* tests (means) for continuous variables and chi-squared tests (%) for categorical variables to ensure randomization success. Any covariates found to differ significantly between groups will be held constant in between-group analyses. A significance level of .05 will be used for tests of all research hypotheses. The outcomes are between-group differences from baseline (T_1_) to post-intervention points (T_2,3_) on psychological and physiological measures. Analyses will be completed using Hierarchical Linear Modeling (HLM). HLM is a flexible approach to analysis of repeated measures data. For example, unlike analysis of variance (ANOVA), linear mixed models do not require that each participant has complete data to be included in the analysis, thus increasing their statistical power [104, 105]. All analyses will be completed using an intention-to-treat (ITT) approach—all participants will be included in the final statistical analysis according to the group (MBCT or TAU) to which they were randomized. To assess the effects of baseline psychological distress on outcomes, separate hierarchical mixed models of each outcome will be conducted using pretreatment psychological distress as a potential moderator.

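### The stated 95 % power does not follow from d = 0.5, two-tailed .05 and 21 women per group for the between-group contrast the trial will test

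*Protocol article*

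**What the plan says.** The Sample size section of the protocol article gives the whole justification in three sentences.

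- Effect: "we expected a medium effect size of Cohen’s *d* = 0.5 [44] for the outcomes of PRA, anxiety, and depression for pre-post testing".
- Test level: "Using a two-tailed test and a .05 significance level".
- Result: "21 participants in each group (42 total) would provide adequate power", with the power put at 95 %.

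It then allows for 20 % attrition. It names no test, no correlation between visits and no repeated-measures model.

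The contrast is fixed elsewhere. The first hypothesis compares MBCT with a treatment-as-usual control group. Statistical analyses says "The outcomes are between-group differences from baseline" to the two later visits, and plans hierarchical linear models. Study design specifies equal allocation. On numbers, the Abstract says "A sample of 60 consenting pregnant women aged 18 years and above will be enrolled".

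**The concern.** Effect size, level, sidedness, group size and power are printed together, so they can be checked against one another. For a comparison of two groups of 21, a half-SD difference is far too small to be found 95 % of the time. The effect is also labelled as a pre-post quantity, which is a within-person scale, whereas the hypothesis is between groups.

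The stake is interpretation. A stated power of 95 % tells readers that a real half-SD benefit would be missed one time in twenty. If the true risk of missing it is several times larger, a non-significant result would be over-read as evidence that MBCT does not work.

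**Working it through.** **Inputs from the protocol article.** d = 0.5, two-sided α = .05, 21 per group, 20 % attrition (Sample size); equal allocation (Study design); between-group contrast (Three hypotheses, Statistical analyses); three visits (Schedule of visits); 60 enrolled (Abstract, Methods).

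**Assumptions, not in the document.** Equal correlation r between any two visits, range 0.5–0.7; the same d at T2 and T3; d in units of the raw outcome SD. Adjusted power uses 2n − 2 degrees of freedom.

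**1. The plan's own figure, as a two-group comparison.** Noncentrality = d√(n/2) = 0.5 × √10.5 = 1.62, with 40 df and critical t 2.02. Power is 35.3 %, not 95 %. At d = 0.5, 80 % power needs 64 per arm and 95 % needs 105. With 21 per arm, 95 % power needs d of about 1.14.

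**2. Reading d as a within-person pre-post effect.** A paired test has noncentrality d√n.
- One arm, n = 21: 0.5 × √21 = 2.29, power 58.7 %.
- Both arms pooled, n = 42: 0.5 × √42 = 3.24, power 88.6 %. This tests change over time, not treatment.

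**3. Baseline-adjusted analyses, 21 per arm.** The effective d is 0.5 divided by the residual SD factor, which is √(1 − r²) for one post visit and √((1 + r)/2 − r²) for the mean of T2 and T3.

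| Analysis | r | Factor | Effective d | Power |
|---|---|---|---|---|
| One post visit | 0.5 | 0.866 | 0.577 | 44.7 % |
| One post visit | 0.7 | 0.714 | 0.700 | 60.0 % |
| Mean of T2 and T3 | 0.5 | 0.707 | 0.707 | 60.9 % |
| Mean of T2 and T3 | 0.7 | 0.600 | 0.833 | 75.0 % |

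To reach 95 %, r must be about 0.90 with one post visit or 0.86 with both.

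**4. Calculations that land near 95 % at N = 42.** Both put the effect on the ANOVA f scale.
- Group-by-time interaction, f = 0.25, three visits, ρ = 0.5: λ = f²Nm/(1 − ρ) = 0.0625 × 42 × 3 / 0.5 = 15.75, with 2 and 80 df, power 94.6 %. For a difference δ at T2 and T3 and none at T1, f = δ/√18, so f = 0.25 means δ = 1.06 SD. With δ = 0.5 (f = 0.118, λ = 3.5), the same test has 35.7 %.
- Between-group main effect, f = 0.5, two visits, ρ = 0.5: λ = f²Nm/(1 + (m − 1)ρ) = 0.25 × 42 × 2 / 1.5 = 14.0, with 1 and 40 df, power 95.5 %. Here d = 2f = 1.0.

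**5. Planned enrolment.** 60/2 = 30 per arm, and 30 × 0.8 = 24 after loss.

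| Analysis | 24 per arm | 30 per arm |
|---|---|---|
| Unadjusted | 39.6 % | 47.8 % |
| One post visit, r 0.5–0.7 | 50–66 % | 59–76 % |
| Mean of T2 and T3, r 0.5–0.7 | 67–81 % | 77–89 % |

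At 24 per arm, the detectable d at 80 % power, unadjusted, is about 0.83.

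**The case against.** The strongest reply is that 35 % belongs to a test the trial does not plan. The article specifies hierarchical linear models over three visits, which can use the baseline and both later visits and can keep women with incomplete data. That stands: a reader might take 35 % as the trial's power, and it is only the unadjusted, single-visit floor. For the same reason 24 per arm is somewhat conservative. But with both post visits and all 30 per arm retained, the result is 77–89 % at the assumed correlations, still short of 95 %, and that is with more women than the 21 for which 95 % is claimed.

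The second reply is that the section cites a power source not available here and names no test, so the figure may come from an undisclosed repeated-measures calculation. That also stands as to origin. The two matches in step 4 suggest a mix-up of f and d, but this is inference. It does not rescue the sentence, because those matches require about twice the stated effect. The 1.06 SD translation itself assumes equal differences at T2 and T3.

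Three stronger readings are tempting and are not supported.

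- *The trial is more likely to miss than to find a benefit.* This is true of the unadjusted test, not of an analysis using both post visits (67–81 % at 24 per arm under the assumptions used).
- *The attrition step is an error.* Dividing gives 21/0.8 = 26.25, hence 27, but 21 × 1.2 = 25.2 also rounds up to 26. The article says "the number of participants required becomes a minimum of 26 participants per group", the gap is one woman per arm, and 60 are to be enrolled.
- *The totals of 52 and 60 conflict.* The first is a minimum and the second a planned enrolment.

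**Conclusion.** The point holds in this form: 95 % power does not follow from the stated effect, level and group size for the between-group contrast. At 21 per arm the figure is about 35 % unadjusted and 45–75 % across the baseline-adjusted analyses examined. The risk of missing a half-SD benefit is therefore about 25–65 %, against the 5 % implied.

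The 35 % rests only on printed inputs. The adjusted figures rest on assumed correlations of 0.5–0.7 and, where both visits are used, on an equal effect at T2 and T3; an effect that fades by three months postpartum would reduce that gain. A correlation of 0.86–0.90 would restore 95 %, but the article states none. This should be corrected, because it is the article's only sample-size justification and the gap is large.

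**What to change.** Delete the 95 % claim. Restate power, or the detectable difference, for MBCT against treatment as usual under the planned longitudinal model, naming the model, the scale of the effect size and the assumed correlation between visits. Base it on the planned 60 with 20 % loss. For d = 0.5 the paragraph could report about 40 % unadjusted, 50–66 % with baseline adjustment and one post visit, and 67–81 % using both post visits (r 0.5–0.7), with a detectable d of about 0.83 unadjusted at 80 % power. A non-significant result should then not be read against 95 % power.

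The cost is rewriting one paragraph and accepting a less favourable stated figure. No participants, visits or analyses are added.

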### Strategies for assessing adherence

To assess adherence with the MBCT homework, we will ask participants to write down the amount of meditation practiced each day, in addition to the type of activity. Home practice records will be collected at the end of each session.

### Statistical analyses

Baseline characteristics (demographic and psychological) will be compared between groups using *t* tests (means) for continuous variables and chi-squared tests (%) for categorical variables to ensure randomization success. Any covariates found to differ significantly between groups will be held constant in between-group analyses. A significance level of .05 will be used for tests of all research hypotheses. The outcomes are between-group differences from baseline (T_1_) to post-intervention points (T_2,3_) on psychological and physiological measures. Analyses will be completed using Hierarchical Linear Modeling (HLM). HLM is a flexible approach to analysis of repeated measures data. For example, unlike analysis of variance (ANOVA), linear mixed models do not require that each participant has complete data to be included in the analysis, thus increasing their statistical power [104, 105]. All analyses will be completed using an intention-to-treat (ITT) approach—all participants will be included in the final statistical analysis according to the group (MBCT or TAU) to which they were randomized. To assess the effects of baseline psychological distress on outcomes, separate hierarchical mixed models of each outcome will be conducted using pretreatment psychological distress as a potential moderator.

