### Inclusion and exclusion criteria

Eligible participants are women over the age of 18 years, who are between 12 and 28 weeks of gestation, with a singleton pregnancy, and who self-identify as experiencing high levels of psychological distress. High psychological distress is defined as a score of 4 or above on the Distress Thermometer – details about screening for psychological distress are presented below [82, 83]. Additional inclusion criteria include the ability to speak, read, and write English. There are several exclusion criteria: current use of antidepressant or anxiolytic medications; a history or current diagnosis of mental disorders with a psychotic, dissociative, hallucinatory, or delusional component; current major depressive disorder, current suicidality, current substance abuse or dependence; an inability to attend each of the classes or to participate in the assessments; and an unwillingness to be randomized.

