### Baseline assessment

If no exclusionary criteria are met, participants will complete a battery of questionnaires assessing a host of demographic (e.g., age, gestational age, marital status, ethnicity, education, household income) and psychosocial (e.g., depressive and anxiety symptoms, positive and negative affect, worry, rumination, life satisfaction, and mindfulness) constructs. After questionnaires are completed, physiological measures will be obtained, including assessments of BP, heart rate variability (HRV), and a stress reactivity task. On the two weekdays immediately following the initial visit, participants’ salivary cortisol will be self-collected via oral swabs and an objective assessment of sleep quality will be obtained via actigraphy. All assessments occur within 2 weeks of participants being randomized to either an MBCT or a control group. All baseline measures will be collected before randomization occurs. A detailed description of all measures is presented below.

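### Adjustment covariates are chosen by significance tests of baseline differences between randomised arms; a pre-specified model should replace this rule

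*Protocol article*

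**What the plan says.** The protocol article, Statistical analyses, states: "Baseline characteristics (demographic and psychological) will be compared between groups using *t* tests (means) for continuous variables", with chi-squared tests for categorical ones. The declared purpose is "to ensure randomization success". The next sentence turns the tests into a modelling rule: "Any covariates found to differ significantly between groups will be held constant in between-group analyses".

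The same section defines the outcomes as between-arm differences from T1 to T2 and T3, analysed by hierarchical linear models. Baseline distress appears again only as a moderator in separate models.

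The candidate variables come from Baseline assessment. It gives demographic examples ("age, gestational age, marital status, ethnicity, education, household income") and eight psychosocial constructs: depressive symptoms, anxiety symptoms, positive affect, negative affect, worry, rumination, life satisfaction and mindfulness. Gestational age is therefore collected, and the eligibility criteria admit women "who are between 12 and 28 weeks of gestation". The Both groups and Randomization and allocation sections describe block randomisation and mention no stratification.

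**The concern.** A significance test between randomised arms asks whether a difference could be due to chance, when valid randomisation already makes that the explanation. A small p-value does not show that randomisation failed, and a large one does not show that it succeeded.

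As a selection rule the test looks at the wrong quantity. Adjustment helps when a variable predicts the outcome, and the between-arm p-value says nothing about that. The rule can bring in an irrelevant variable flagged by chance and leave out a predictor whose imbalance falls short of the threshold.

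The adjustment set for every outcome is then unknown until the data are seen. There is also a loose end. The psychological baselines tested appear to include scales that are primary outcomes. If one is flagged, its T1 value could enter the model as a covariate while T1 is already part of the response, and the text does not settle this.

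**Working it through.** The plan attaches no figure to this rule, so there is none to reproduce. Its sample-size section only supplies arm sizes and an effect size.

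**Inputs**
- Arm size: 26 (Sample size, minimum per group, 52 in total) and 30 (half of the 60 in the Abstract, equal allocation).
- Candidates: 6 demographic + 8 psychosocial = 14. Both lists are given as examples, so the number is open.
- Threshold: none is stated for the baseline tests. I assume .05 two-sided, by analogy with "A significance level of .05 will be used for tests of all research hypotheses" and "Using a two-tailed test and a .05 significance level".
- Effect: d = 0.5 (Sample size). The documents give no correlations; all of those below are assumed.

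**1. Chance of at least one flag under valid randomisation**, 1 − 0.95^k for independent variables:
- k = 6: 26 %
- k = 14: 51 %
- k = 20: 64 %

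Positive correlation among the psychosocial scales would lower these figures.

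**2. What gets flagged.** Suppose 2 of the 14 predict outcome and 12 do not. The chance that either predictor is flagged is 1 − 0.95² = 10 %; for any of the other 12 it is 1 − 0.95¹² = 46 %. A simulation with 10,000 trials per scenario at 26 per arm gave about 10 % and 46 %.

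**3. Smallest imbalance flagged**, t(.975, 2n − 2) × √(2/n):
- n = 26: 2.009 × 0.277 = 0.56 SD
- n = 30: 2.002 × 0.258 = 0.52 SD

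**4. Validity.** In the same simulation with no true effect, the rule applied to change scores rejected in 4.3 % and 4.4 % of trials, and the mean estimate was zero to within simulation error. A fixed covariate set rejected in 5.0 % and 5.2 %.

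**5. Precision** at 26 per arm and true d = 0.5 (SE in SD units, power in brackets):

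| Assumed correlation with post-score (T1 score, gestational age) | Change score, no covariates | Change score, test-selected covariates | T1 score and gestational age fixed |
|---|---|---|---|
| 0.5, 0.2 | 0.276 (42 %) | 0.276 (40 %) | 0.237 (54 %) |
| 0.6, 0.3 | 0.248 (50 %) | 0.248 (47 %) | 0.208 (64 %) |

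The selection step itself costs about 2 to 3 points of power. Most of the gain comes from conditioning on T1 instead of subtracting it. In closed form the SE is √(2/26) = 0.277 times √(2(1 − r)) for change and √(1 − r²) for covariance adjustment:
- r = 0.5: 0.277 against 0.277 × 0.866 = 0.240
- r = 0.6: 0.277 × 0.894 = 0.248 against 0.277 × 0.800 = 0.222

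The remaining gain is from gestational age, which the simulation drew as independent of the T1 score, so that it predicts change by construction. Both calculations use a single post-baseline visit.

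**6. How a covariate enters matters.** In 40 simulated complete datasets (26 per arm, three visits, random intercept, covariate correlated 0.5 with outcome, imbalance 0.5 SD), adding the covariate as a main effect left the group-by-time estimate unchanged to numerical precision and its SE at 0.277. A stable covariate affects that contrast only if T1 is conditioned on or if it interacts with time.

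**The case against.** The strongest reply is that the planned analysis already protects against much of the feared harm, and that most of it stands.

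- A reader might infer that an unflagged imbalance leaves 0.26 to 0.28 SD of bias, about half the planning effect (0.52 or 0.56 SD × an assumed correlation of 0.5), and that fixed adjustment would cut residual variance by 25 %. Those figures describe an unadjusted comparison of post-scores. The protocol's outcomes are differences from T1, so a covariate that shifts T1 and T2 equally cancels (step 6). The correlation of 0.5 has no source in the document.
- A reader might infer that the rule invalidates the test or biases the result. It does neither on average (step 4); it is slightly conservative.
- A reader might infer that gestational age bears on cortisol, sleep and the primary scales. The Background says only that cardiovascular stress reactivity declines as pregnancy progresses. That bears on a secondary hypothesis; nothing ties gestational age to the primary outcomes.
- This is a condensed article, and a fixed covariate list could sit in an analysis plan not shown. The Simultaneous interventions section also allows for another adjustment, for adjunctive therapies. The lack of a list is therefore not the point.

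What the reply does not reach is the rule that the article does state. Nothing else in the document replaces it.

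**Conclusion.** The concern holds in a limited form. The protocol selects covariates by a criterion that reflects chance and ignores relation to outcome, and it gives the baseline tests a purpose they cannot serve. The chance of at least one flag is about 51 % for 14 variables, given independence and a .05 threshold, neither of which the document states. An imbalance below 0.52 to 0.56 SD is never acted on.

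The consequences are an adjustment set that depends on the data and lost precision in a trial of 52 to 60 women. Under the assumed correlations, power at 26 per arm is 40 to 47 % with the rule on change scores and 54 to 64 % with a fixed set, the larger part of the gap coming from how T1 is used. There is no inflation of type I error and no bias on average. The change should be made, but the rule does not make the trial's conclusions invalid.

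**What to change.** 1. Report baseline characteristics descriptively by arm. Delete the baseline tests and the significance-triggered adjustment.
2. Pre-specify the model and use the T1 score once: either as a covariate with T2 and T3 as responses, or as a response with a baseline mean common to both arms. Doing both would use T1 twice.
3. Pre-specify gestational age at baseline at least for the cardiovascular outcomes, entered so that it can act on the post-baseline contrast: with T1 conditioned on, or with a covariate-by-time term. Its value for the psychological outcomes is an assumption and should be described as such if it is included there.
4. Randomisation batch may be included, for example as a random effect, because women are randomised once enough have completed baseline to form a group (Both groups section).

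The cost is wording in the protocol or analysis plan. T1 scores and gestational age are already collected and take one slope each when T1 is a covariate; a covariate-by-time term takes more. The cost of batch depends on the number of batches, which is not stated. Recruitment was still open and no interim analysis was planned, so the change could be made before outcome data are analysed.
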